## Discussion

Non-AIDS comorbidities are frequently encountered in the routine care of PLWHIV. As the number of PLWHIV has increased, and this population continues to age, information on the burden of comorbidity and potential risk factors leading to disease is warranted. The current study is an observational and longitudinal cohort study. It includes several clinical measures and is conducted in parallel to a large control cohort (CGPS) from the same geographical area using uniformly collected data. The primary goal is to identify the burden and the determinants of non-AIDS comorbidity. Primary outcome measures are characterized with respect to three biological systems, i.e. cardiovascular, respiratory, and hepatic non-AIDS comorbidity. Beyond the primary research questions, this study will establish a biobank for future prospective studies to assess pathogenesis of comorbidity in HIV infection.

Despite numerous studies on non-AIDS comorbidity, many questions remain: What is the burden of disease in the current cART era and which mechanisms are at play? What is the optimal clinical care, screening, and monitoring of patients with comorbidities? How does socioeconomic status affect development and prognosis on comorbidity? How will cART be tolerated in the elderly and what are the effects of polypharmacy in the elderly? In 2030, 28% of PLWHIV are expected to have three comorbidities or more, and 54% will be prescribed co-medication [3]. Most randomized trials of cART have, however, excluded elderly PLWHIV or those with comorbidities, and there is a continuous need to track non-AIDS comorbidity in non-interventional studies.

This study has *a priori* been designed to assess non-AIDS comorbidities. Thus, one of the main strengths is the multimodal assessment of risk factors associated with non-AIDS comorbidity. This will also be one of the largest cohort studies with assessment of non-AIDS comorbidity using clinical measured endpoints. Other cohort studies that are ongoing with use of various clinical examinations, include the Multicenter AIDS cohort study (MACS) [45], Women’s interagency HIV study (WIHS) [46], the AIDS linked to intravenous experience (ALIVE) study [47], all from the United States, the cohort from a HIV metabolic clinic in Italy [4], and most recently the AGE_H_IV cohort study from the Netherlands [48]. Besides the use of a control cohort with uniformly collected data, a main strength also includes the use of Danish registry data. These registries will allow linkage of data from the COCOMO study cohort to complete information on cause and date of death, hospital discharge, and of prescription medicine.

A weakness includes selection bias such as healthy volunteer bias, as those with serious illness or disability may be less likely to participate. Non-participation may include individuals that have difficulty attending on-site examinations (e.g. IDUs, elderly, home- or nursing home-bound). CGPS participants are recruited at random whereas COCOMO participants are recruited at their regular ambulatory visits. Exact reasons for non-participation will not be registered. However, the number of non-participaters will be registered, and to some extent, it will be possible to compare the non-participators with the participators, e.g. in respect to age, gender, CD4 count, and viral load. All PLWHIV registered as out-patients at the two sites receive an invitation to participate. Advertisement is found at the Patient Organization HIV Denmark (www.hiv-danmark.dk) and as posters at the two sites.

As the study collects information on some early life events through self-reports (i.e. exposure to passive smoking, childhood respiratory infections), a recall-bias cannot be precluded. However, few non-AIDS comorbidity studies have previously collected such information. Although the study is large, a sample size of 1500 PLWH precludes the study from examining rare clinical diagnoses such as specific non-AIDS cancers. A loss to follow up is anticipated for the clinically measured endpoints, and has been taken into account in power analysis. Finally, the study is confined to a restricted geographic area with individuals of primarily Western European descent, and although broad eligibility criteria are used, results may not be generalizable to other parts of the world.

In conclusion, the spectrum of disease in PLWHIV has changed and non-AIDS comorbidity will be more common as this population continues to age. This will have implications for the clinical care and continue to put new demands on health authorities. This study has the potential to identify novel risk factors for comorbidity in PLWHIV that may be used to guide future interventional studies. Guidelines on screening and monitoring of non-AIDS comorbidity continue to evolve and may help to reduce the burden of non-AIDS comorbidity. Use of data will be confined to the study group, but potential collaborators or request for data can be submitted at [contact].

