**Methods/design:**

The Copenhagen comorbidity in HIV-infection (COCOMO) study is an observational, longitudinal cohort study. The study was initiated in 2015 and recruitment is ongoing with the aim of including 1500 PLWHIV from the Copenhagen area. Follow-up examinations after 2 and 10 years are planned. Uninfected controls are derived from the Copenhagen General Population Study (CGPS), a cohort study including 100,000 uninfected participants from the same geographical region. Physiological and biological measures including blood pressure, ankle-brachial index, electrocardiogram, spirometry, exhaled nitric oxide, transient elastography of the liver, computed tomography (CT) angiography of the heart, unenhanced CT of the chest and upper abdomen, and a number of routine biochemical analysis are uniformly collected in participants from the COCOMO study and the CGPS. Plasma, serum, buffy coat, peripheral blood mononuclear cells (PBMC), urine, and stool samples are collected in a biobank for future studies. Data will be updated through periodical linking to national databases.

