## Methods/design

### Study design

The COCOMO study is a non-interventional, observational, longitudinal study initiated in March 2015. The study aims to enroll up to 1500 PLWHIV from two sites in Copenhagen (Rigshospitalet, University of Copenhagen, and Hvidovre Hospital, University of Copenhagen). Uninfected controls will be derived from the Copenhagen General Population Study (CGPS) with a study population of more than 100,000 participants from the greater Copenhagen area [30, 31]. An overview of physical measurement and collection of biomaterial (Table 1), hematological and biochemical measures (Table 2), and content of questionnaire are given (Table 3).

**Table 2 Tab2:** Hematological and biochemical measures

Measurements	Description
Hematology	Hemoglobin, hematocrit, leucocytes, differential count, thrombocytes, red cell dimensions
Electrolytes and iron metabolism	Sodium, potassium, calcium, iron, magnesium, ferritin, transferrin
Liver/ organ related	Aspartate aminotransferase, alanine aminotransferase, alkaline phosphatase, bilirubin, gamma glutamyltransferase, albumin, antitrypsin, amylase, creatinine kinase, lactate dehydrogenase
Coagulation	Activated partial thromboplastin time, coagulation factor II+ VII+ X, D-dimer, fibrinogen
Lipids	Total cholesterol, remnant cholesterol, HDL-cholesterol, LDL-cholesterol, triglycerides, adiponectin, lipoprotein, apolipoprotein A, B, and E
Metabolic	Glucose, HbA1c, ethanol
Renal function	Creatinine, urea, uric acid
Thyroid function	Thyroid stimulating hormone, free T3/T4
Immunology	Immunoglobulin A and E, rheumatoid factor IgM, complement C3
Inflammation	High sensitivity C-reactive protein

All measures are analyzed uniformly in the Copenhagen co-morbidity (COCOMO) study cohort and in the Copenhagen general population study (CGPS) at Biochemical Department, University Hospital Herlev, Copenhagen

**Table 3 Tab3:** Overview of variables recorded by questionnaires

Variable	Examples
External risk factors	
Smoking	Current, previous, and passive smoking, cumulative pack-years, type, filters, e-cigarettes
Alcohol/drug abuse	Current and previous alcohol intake, intravenous drug use, cannabis, methadone treatment
Biomass fuel/environmental exposure	Occupational dusts, organic, inorganic gasses, vapors, and fumes (outdoor and indoor)
Demographics	Ethnicity, nationality, marital status, children
Education/income	Level of education, house-hold income
Work	Employment, income, night work

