### Participants

#### Eligibility criteria

To be eligible for the COCOMO, study participants must be a minimum age of 18 years, infected with HIV-1, out-patient at either Department of Infectious Diseases at University Hospital Copenhagen or Hvidovre University Hospital, and be able to sufficiently understand oral and written study information in Danish or English to provide an informed consent. Insufficient knowledge of the Danish language does not exclude individuals if questionnaires can be filled out by the help of relatives or staff. Contraindications to the various measures performed in the study (i.e. renal impairment or contraindications to beta blocking agents used for CT angiography) do not exclude a participant from other parts of the study. In total, 4500 PLWHIV are eligible for inclusion. This number comprises ~95% of PLWHIV in Eastern Denmark/Zealand (inhabited by approximately 2,5 mill people). To be eligible for participation in the CGPS, individuals must be a minimum of 20 years of age and reside in the greater Copenhagen area. Starting from 2014 a large number of the first 100,000 participants from the CGPS were re-invited by regular mail. Of all inhabitants in the selected area, 25% of the 20–40 years old and 100% of the >40 years old are invited. A random sample of approximately 10,000 individuals above 40 years of age will have an unenhanced coronary artery calcium score (CACS) and CT angiography of the heart, and approximately 2000 will, in addition, have a CT scan of the chest and upper abdomen as described under methods. Scanning protocols in the COCOMO and CGPS studies are identical.

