### Planned statistical analysis

Prevalence and risk factors for non-AIDS comorbidity will be calculated based on baseline data. For some outcome data we plan to match PLWHIV with uninfected control 1:5 on age and gender. Student’s *t*-test, Mann-Whitney *U*-test and Pearson’s chi-squared test and appropriate uni- and multivariate regression analyses will be used at baseline. For prospective studies, Cox regression, Kaplan-Meier curves, log-rank test, and mixed effects models will be used. In general, missing data is expected to be low and multiple imputations not likely to be required. Characteristics for loss-to follow up will be assessed.

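### At most a third of eligible PLWHIV are to be enrolled, and the plan describes no prevalence estimate standardised to the clinic population, although frame data on non-participants are partly obtainable

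*Protocol article*

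**What the plan says.** The Abstract gives prevalence and incidence of non-AIDS comorbidity among PLWHIV in Denmark as the aim. Study objectives and Discussion repeat burden of disease as a main goal.

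- **Frame.** Eligibility criteria: "In total, 4500 PLWHIV are eligible for inclusion". This is put at about 95% of PLWHIV in Eastern Denmark/Zealand.
- **Invitation.** Discussion: "All PLWHIV registered as out-patients at the two sites receive an invitation to participate".
- **Target.** Study design: "The study aims to enroll up to 1500 PLWHIV from two sites in Copenhagen". The Abstract adds that "recruitment is ongoing with the aim of including 1500 PLWHIV from the Copenhagen area".
- **Expected selection.** Discussion: "A weakness includes selection bias such as healthy volunteer bias, as those with serious illness or disability may be less likely to participate". It also names illicit drug users, the elderly and people bound to home or nursing home. Exact reasons for not taking part will not be recorded, but the number of non-participants will be.
- **Data on non-participants.** Discussion, with the qualifier that this holds only to some extent: "it will be possible to compare the non-participators with the participators, e.g. in respect to age, gender, CD4 count, and viral load".
- **Analysis.** Planned statistical analysis: "Prevalence and risk factors for non-AIDS comorbidity will be calculated based on baseline data". The section then lists 1:5 matching to controls on age and gender for some outcomes, tests, regression, and the handling of missing data and loss to follow-up. It mentions no weighting or standardisation to the 4500 and rules none out.

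**The concern.** A prevalence meant to describe PLWHIV is to be calculated from a volunteer sample that leaves at least two thirds of the frame unobserved. The article expects non-participants to be older and sicker, groups that plausibly carry more comorbidity, so the reported burden would probably be too low. The interval around the estimate reflects sampling error only and says nothing about this.

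The study expects to hold, at least in part, four variables on non-participants. One of them, age, corresponds to a selection mechanism the article names, and the article itself links comorbidity to ageing. A comparison table shows that the groups differ but does not move the estimate. The same variables could be used to standardise it.

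**Working it through.** **Inputs from the article:** target 1500 (Study design), frame 4500 (Eligibility criteria). It gives no participation rate, no prevalence and no prevalence precision, so there is no stated figure on this point to reproduce. The one sample-size calculation shown concerns FEV1 decline. It reproduces (739 PLWHIV and 2956 controls, against approximately 750 and 3000) and does not bear on this point.

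**Step 1, share of the frame.** 1500/4500 = 33.3%. Since 1500 is an upper limit, this is a ceiling, and at least 3000 people (66.7%) stay outside the sample.

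**Step 2, total selection bias.** With p1 the prevalence in participants and p0 in the rest, frame prevalence = p1/3 + 2·p0/3. The error of the crude estimate is p1 − (p1/3 + 2·p0/3) = (2/3)(p1 − p0).

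**Step 3, comparison with sampling error (assumed prevalences, n = 1500).** At p1 = 10% the 95% half-width is 1.96 × √(0.10 × 0.90/1500) = 1.5 points. The bias equals this when the gap is 1.5 × 1.52 = 2.3 points, that is p0 = 12.3%, a ratio of about 1.23.

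| p1 (assumed) | p0/p1 (assumed) | Frame prevalence | Understatement | Half-width |
|---|---|---|---|---|
| 10% | 1.0 | 10.0% | 0 | 1.5 |
| 10% | 1.25 | 11.7% | 1.7 | 1.5 |
| 10% | 1.5 | 13.3% | 3.3 | 1.5 |
| 10% | 2.0 | 16.7% | 6.7 | 1.5 |
| 20% | 1.25 | 23.3% | 3.3 | 2.0 |
| 20% | 1.5 | 26.7% | 6.7 | 2.0 |

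**Step 4, what weighting could recover (assumed).** Take two age strata, each half of the frame, with prevalences 5% and 20%. The true frame value is 12.5%.

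- Participation 40% and 26.7%: crude = (0.40 × 5 + 0.267 × 20)/(0.40 + 0.267) = 11.0%. Weighting returns 12.5%, a shift of 1.5 points. Kish design effect 1.04, effective n about 1440.
- Participation 45% and 21.7%: crude = 9.9%. Weighting returns 12.5%, a shift of 2.6 points. Design effect 1.14, effective n about 1316.

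In these examples all selection runs through age, so weighting recovers everything. In practice it recovers only the part explained by the variables used.

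**Step 5, cost in precision.** Interval width grows with the square root of the design effect: √1.1 = 1.05 and √1.5 = 1.22, so about 5 to 22% wider.

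**The case against.** The strongest objection is that this argues from silence. The text comes from a limitations paragraph and a one-paragraph analysis summary in a condensed article. Participation weighting is commonly left to a full protocol or SAP, which is not shown. The article discloses the bias and contains no wrong figure here. This stands. A reader might infer that the non-participant data are used solely for description and that prevalence will remain uncorrected. The article does not say so: comparison is merely the only use it describes.

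Four further points limit the strength of the concern:

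- **One third is not an observed participation rate.** It is a target ceiling while recruitment is ongoing. If enrolment stops at the target, some of the remaining 3000 may never have declined.
- **The frame data are promised only in part.** Other data sources and Discussion describe record retrieval and registry linkage for the COCOMO study and its cohort, not for non-participants. A participation model over all 4500 may therefore need individual data that the text does not promise.
- **Most named mechanisms are out of reach.** Of serious illness, disability, drug use, being home-bound and age, only age is among the four variables. A weighted figure could look corrected while much of the selection remains.
- **There is a second selection step.** Contraindications and the pulse limit for CT angiography, and the validity criteria for elastography, reduce the number measured. The half-widths above, at n = 1500, are then too narrow for those outcomes, and weights for participation do not cover this step.

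AIM 1's contrast with uninfected persons is also not what this point addresses. The point concerns absolute prevalence in PLWHIV. None of this removes the case for a secondary estimate where the data exist, because absolute prevalence is a stated aim and age-related selection is expected.

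**Conclusion.** The point holds as a cheap improvement to the prevalence estimates, not as an established error. The documents establish a ceiling of 33% enrolment from the frame, expected under-participation by the elderly and the seriously ill, partly obtainable frame variables, and no described step that carries those variables into the prevalence estimate.

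The size of the correction is unknown, because the article gives neither prevalence nor participation by subgroup. It would be tempting to read the 3.3 points (10% against 15%) as the gain from weighting. It is not: it is the total selection bias under an assumed gap, and weighting would remove an unknown part of it. With no gap there is no bias. At 10% prevalence, a ratio below about 1.23 gives a bias smaller than the half-width at n = 1500.

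**What to change.** In Planned statistical analysis, add a secondary prevalence estimate for PLWHIV:

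- Post-stratify or rake participants to the eligible clinic population on age and gender, and on CD4 count, viral load and site where frame data allow. Use inverse-probability-of-participation weights only if individual-level data on non-participants exist.
- Report it beside the unweighted estimate for the primary outcomes expressed as prevalences. Spirometric indices analysed as continuous measures need not be included.
- Keep the COCOMO–CGPS contrast unweighted as the main analysis, since the controls carry their own selection.
- State that weighting removes only selection explained by these variables. Selection by illness, disability and drug use, and selection into valid CT or elastography measurement, remains.

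If the full protocol or SAP already contains such a step, a sentence saying so is enough. Otherwise the cost is analysis work on frame data the study expects to hold in part, plus a somewhat wider interval for the secondary estimate (about 5 to 22% for an assumed design effect of 1.1 to 1.5). No change to recruitment or measurements is needed.

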## Abbreviations

ABI: Ankle-brachial index
APRI: AST to platelet ratio index
CACS: Coronary artery calcium score
cART: Combination anti-retroviral therapy
CGPS: Copenhagen general population study
COCOMO: Copenhagen comorbidity in HIV-infection study
COPD: Chronic obstructive pulmonary disease
CT: Computed tomography
CVD: Cardiovascular disease
ECG: Electrocardiography
eNO: Exhaled nitric oxide
HCV: Hepatitis C-virus
HIV: Human immunodeficiency virus
IDU: Illicit drug use
LRD: Liver related disease
MI: Myocardial infarction
NAFLD: Non-alcoholic fatty liver disease
NASH: Non-alcoholic steatohepatitis
PAD: Peripheral arterial disease
PBMC: Peripheral blood mononuclear cells
PCP: *Pneumocystis* pneumonia
PLWHIV: People living with HIV
TE: Transient elastography
